### Study data management, oversight, and publication

Data will be handled confidentially. Data will be collected in the electronic patient file by the local researcher and subsequently registered in Castor EDC, Amsterdam, the Netherlands. Patients will be anonymized. The handling of personal data will be performed in compliance with the Dutch Personal Data Protection Act and in compliance with Good Clinical Practice guidelines. Data will be kept for 15 years. Informed consent from study participants will be recorded at every hospital in the electronic patient file, and signed paper forms will be securely locked away within the hospital where the patient is undergoing treatment.

The study is monitored by an independent monitoring company (Julius Clinical, Zeist, the Netherlands) according to a detailed monitoring plan. Insurance is provided for all participants in accordance with Dutch legislation. The results of this study will be submitted to peer-reviewed journals.

## Discussion

This study is designed to give a more decisive answer to the question of whether a dangling protocol is necessary after a free flap reconstruction of the lower leg. This will be the first randomized controlled study comparing a non-dangling protocol to a dangling protocol. Worldwide, the current standard of care is a dangling protocol. We believe that the length of hospitalization in a non-dangling protocol can be significantly reduced compared to that for a dangling protocol. This would potentially reduce infection rates and lower costs. Furthermore, patients undergoing a non-dangling protocol will be able to ambulate at an earlier stage, reducing the risk of deep vein thrombosis and pulmonary embolism.

Our POCT measurements are a novel way to provide us with detailed information about the gaseous changes in a free flap during dangling. Furthermore, we will be able to give more insight into the physical functions, infection rates, and osseous union rates for this patient group.

At the end of this study we will have included 130 patients. This will be the largest prospective study in this patient group. Therefore, we will also be able to collect unique data about the physical functions, infection rates, and union rates.

### Limitations

Given that this is a non-blinded study, patients who are randomized to the no-dangling group could implement a dangling protocol on their own. To prevent this, we will provide patients in this group with a step counter, and they will have to keep track of the amount of time that their leg was in a dangling position.

For ethical reasons, we believe that it is important that the treating physician can decide to withdraw a patient from the dangling part of the study if the physician thinks the risk of flap necrosis is too high. However, this could lead to treatment indication bias. However, we should be able to account for this by intention-to-treat or per protocol analysis.

Our sample size calculation is based on a rate of partial flap loss of 6%. We decided that a rather high absolute increase in incidence of 12% would be clinically significant. If we had chosen a lower increase of incidence the sample size would have increased significantly, resulting in a non-feasible study.

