## Methods/design

### Trial design

The study is taking place at three Dutch hospitals: University Medical Center (UMC) Utrecht, Erasmus University Medical Center (Erasmus MC) Rotterdam, and UMC Groningen. A dangling protocol is the current standard of care in these hospitals. Patients are randomly assigned by a computer program to group A or B. Patients in group A start a dangling protocol on POD 7. Patients in group B can mobilize without limitations starting on POD 7 and are discharged from the hospital when possible. All patients will be seen on POD 12–15, after 5–7 weeks, 2.5–3.5 months, and 5–7 months at the ward or the outpatient clinic. During these visits the complications will be evaluated. The study phases and data collection time points are shown in Fig. 1. The Standard Protocol Items: Recommendations for Interventional Trials (SPIRIT) checklist is provided as Additional file 1.

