### Sample size calculation

Based on the incidence of partial flap necrosis in the meta-analysis by Xiong et al., we performed a power calculation [8]. Because total free flap loss rarely occurs after POD 5, we decided to focus in this study on partial flap loss. Based on a rate of partial flap loss of 6%, we decided that an absolute increase in incidence of 12% would be clinically significant. To detect this non-inferiority margin with 80% power and a two-sided 95% confidence interval (CI) and 5% estimated loss to follow-up, we aim to include 130 patients. Each year about a hundred lower limb reconstructions are performed at our three hospitals, resulting in an inclusion time of 2 years.

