### Statistical analysis

As the primary hypothesis we will calculate the absolute risk differences in incidence of partial flap loss (major and minor combined) between groups. If the upper limit of the 95% CI falls within 12%, we regard this as a non-inferiority difference.

The secondary hypotheses will be tested for superiority: absolute risk difference for one or more major complications and 95% CI, and linear regression for length of stay, physical function, and blood tests.

We will perform an intention-to-treat analysis. However, since investigators can decide to withdraw a subject from the study for life-threatening medical reasons (see the subsequent section on Recruitment, consent, and withdrawal), we will perform an additional per protocol analysis and compare baseline characteristics of patients withdrawn and patients lost to follow-up. We will use multiple imputation to account for missing variables.

We will perform an interim analysis when 40 patients are randomized. If we find a significant difference through Fisher’s exact test in patients having one or more major or minor complications, we will terminate the trial. Based on previous studies, we will test our final non-inferiority hypothesis without alpha adjustment for the superiority tested interim analysis.

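### Per-protocol analysis cannot account for surgeons withdrawing high-risk flaps, and the withdrawal text leaves it unclear whether those flaps stay in the intention-to-treat primary analysis

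*Protocol article*

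**What the plan says.** Four places in the protocol article bear on this.

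- **Statistical analysis, decision criterion.** The risk difference in partial flap loss is judged as follows: "If the upper limit of the 95% CI falls within 12%, we regard this as a non-inferiority difference". The sentence names no analysis set.
- **Statistical analysis, sets.** "We will perform an intention-to-treat analysis". Then, because investigators may withdraw a subject for life-threatening reasons, "we will perform an additional per protocol analysis and compare baseline characteristics of patients withdrawn and patients lost to follow-up". Multiple imputation is planned for missing variables.
- **Recruitment, consent, and withdrawal.** Beyond the life-threatening reasons there are two further routes. The treating physician may take a patient in either group off the dangling part if total flap necrosis looks very likely; the text keeps that patient for the secondary objectives and does not mention the primary one. A patient whose adverse event prevents either regimen is removed from the primary outcome and kept for the secondary objectives if possible.
- **Limitations.** The article admits that physician withdrawal could bring in treatment indication bias, and answers: "However, we should be able to account for this by intention-to-treat or per protocol analysis".

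**The concern.** The decision to withdraw is made after randomisation, by a physician who knows the allocation, on the expectation that the flap will do badly. Leaving such patients out conditions on a forecast of the outcome. A per-protocol analysis that does so creates the bias it is offered to cure. The intention-to-treat half of the claim is sound only if that analysis really contains everyone, and the withdrawal section puts this in doubt.

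If leaving out dangling does cause more flap loss, group B has more failing flaps to withdraw, even when physicians apply one standard to both groups. The observed difference then shrinks towards zero. In a non-inferiority trial that favours the new policy: a harmful effect is more likely to be declared acceptable, and a practice that is standard in these hospitals could be dropped on that result.

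**Working it through.** **1. Reproduce the planned size.** Inputs from Sample size calculation: 6% loss rate and 12-point margin ("Based on a rate of partial flap loss of 6%, we decided that an absolute increase in incidence of 12% would be clinically significant"). The same section sets power at 80%, a 95% interval that is two-sided, losses of 5% and a target of 130. Allocation is taken as 1:1, since Trial design says only "Patients are randomly assigned by a computer program to group A or B".

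n per arm = (1.960 + 0.8416)² × 2 × 0.06 × 0.94 / 0.12² = 7.849 × 0.1128 / 0.0144 = 61.48, so 62. Total 2 × 61.48 / 0.95 = 129.4, so 130 (131 if each arm is rounded up first). The stated 130 reproduces, and 62 evaluable per arm is used below.

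**2. How few flaps it takes.** Wald upper limit = pB − pA + 1.96 × √[pA(1−pA)/nA + pB(1−pB)/nB].

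- All kept, 4/62 v 7/62: 4.8 + 10.0 = 14.8 points. Fails (Newcombe 15.8, fails).
- Two lost group B flaps dropped, 4/62 v 5/60: 1.9 + 9.3 = 11.2. Passes (Newcombe 12.4, fails).
- Three dropped, 4/62 v 4/59: 0.3 + 8.9 = 9.2. Passes (Newcombe 10.5, passes).

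**3. Error rate when the true harm equals the margin.** True rates 6% v 18%; the same share f of flaps that will be lost is dropped in both arms, and no others. The rate left in an arm is p(1−f)/(1−fp). For f = 50% this is 0.09/0.91 = 9.9% in B and 0.03/0.97 = 3.1% in A, a difference of 6.8 points instead of 12. Chance of an upper limit below 12 points, by simulation:

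| Share f dropped | Difference left | Wald | Newcombe |
|---|---|---|---|
| 0 (all kept) | 12.0 | 3.6% | 2.5% |
| 10% | 11.1 | 5% | 3% |
| 25% | 9.6 | 9% | 6% |
| 33% | 8.7 | 13% | 8% |
| 50% | 6.8 | 27% | 15% |

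At f = 25% the expected number dropped is 62 × 0.06 × 0.25 = 0.9 in A and 62 × 0.18 × 0.25 = 2.8 in B.

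**4. Sensitivity to the assumptions (Wald).** With f = 25% and 10% of the flaps that would have survived also withdrawn, the figure is 6.6%. If withdrawal is unrelated to outcome (25% of both kinds), it is 3.7%, so there is no inflation. If only group B flaps are withdrawn, it is 13% at f = 25% and 41% at f = 50%.

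**5. Can the intention-to-treat set lose the same flaps?** Set side by side, Statistical analysis promises intention-to-treat, while Recruitment, consent, and withdrawal takes adverse-event patients out of the primary outcome and mentions only secondary objectives for high-risk withdrawals. Both cannot hold as written for the adverse-event group. For the high-risk group the text is silent on the primary outcome.

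**The case against.** Several points on the other side stand.

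- **The order of the analyses.** A reader might infer that no rule chooses between the sets, or that a pass in either would do. The documents do not support that. Statistical analysis makes intention-to-treat the planned analysis and per protocol an addition; the word suggesting a choice occurs only in the Discussion. What is absent is an explicit tie between the criterion and a set. A rule for discordant results may well sit in an analysis plan that is not shown, and its absence is not counted here.
- **The per-protocol set.** A reader might also infer that it certainly drops exactly the flaps that will be lost. It is not defined in the article, so their exclusion is an inference, though a natural one for patients taken off the regimen.
- **Overlap with the endpoint.** The withdrawal trigger is expected total necrosis (Limitations says only flap necrosis), whereas the endpoint is partial loss. Nothing shows that a quarter or a half of eventual losses would be foreseen and withdrawn. At a tenth, the effect is small.
- **The stated reason.** Statistical analysis justifies per protocol by withdrawals for life-threatening reasons, a route listed separately from flap-risk withdrawal. It is Limitations that offers it as the answer to flap-risk withdrawal.
- **Direction.** If more failing flaps were withdrawn from group A, the bias could run the other way.

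Multiple imputation does not settle the matter: the article does not say that it covers patients removed from the primary outcome, whose result can often be observed directly.

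**Conclusion.** The concern holds in limited form. The statement that per-protocol analysis accounts for indication bias is wrong as a matter of method, and needs no arithmetic. The sections on statistical analysis, withdrawal and limitations also do not agree on who is in the primary analysis, so prognosis-selected flaps could be missing from the analysis called intention-to-treat as well as from the per-protocol one.

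The size is illustrative. For a true difference at the margin, false non-inferiority rises from 3.6% to between 5% and 27% (Wald), or from 2.5% to between 3% and 15% (Newcombe), for assumed shares from 10% to 50%. The article gives neither the share nor the interval method. The inflation is smaller if many flaps that would survive are also withdrawn, and it affects the conclusion only if a reduced set carries the verdict. If intention-to-treat with every randomised patient decides, the per-protocol result cannot reverse it.

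**What to change.** Reconcile the three sections as follows.

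1. **Statistical analysis:** state that the 12-point criterion is applied to the intention-to-treat set of all randomised patients. Patients taken off their regimen for flap risk or a flap-related event are analysed in their allocated arm with their observed 6-month outcome.
2. **Recruitment, consent, and withdrawal:** separate leaving the regimen from leaving the primary analysis, and remove the wording that ends participation in the primary outcome after an adverse event. The physician's freedom to take a patient off the regimen is not touched.
3. **Per-protocol analysis:** label it supportive only, and do not let it exclude patients for flap-risk or flap-event withdrawal.
4. **Limitations:** delete the claim that per-protocol analysis accounts for indication bias.

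Requiring non-inferiority in both sets is optional; statisticians differ on that convention, and the correction does not depend on it.

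The cost is a few sentences. No new patients or data are needed: complications are already assessed to 6 months, and withdrawn patients are already meant to stay for the secondary objectives. The result will look somewhat less favourable if withdrawn flaps fail.

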### Trial status

The study was registered at the CCMO (Central Committee on Research Involving Human Subjects) in the Netherlands on 11 July 2018 (NL63146.041.17) and registered with the Netherlands Trial Register (registration number NTR7545). This article is based on protocol version number 7.0, dated 22 January 2019. Recruitment started at the UMC Utrecht on 16 October 2018, at the Erasmus MC Rotterdam on 17 January 2019, and at the UMC Groningen on 29 January 2019. The approximate date on which recruitment will be completed is 1 July 2021.

## Data Availability

Data sharing is not applicable to this article, as no datasets will be generated or analyzed during the current study.

## Abbreviations

CCMO: Centrale Commissie Mensgebonden Onderzoek
EQ-5D: EuroQol five dimensions
POCT: Point-of-care testing
POD: Postoperative day
PROMIS: Patient-Reported Outcomes Measurement Information System
UMC: University Medical Center
VAS: Visual analog scale
